## Abstract

**Background:**

The health of a woman before conception not only influences the outcome of her pregnancy but also the lifelong health of mother and child. Many women in the UK are inadequately prepared for pregnancy, with reports of a high prevalence of smoking, low folic acid supplement use, and suboptimal diet and physical activity. Get Ready! will link an online digital tool to identify women planning pregnancy most at risk of complications with a personalised intervention to improve health behaviours and biomarkers of metabolic health.

**Methods:**

Women planning pregnancy will be identified from a free and widely used online preconception tool. A short online screening questionnaire will then be used to recruit women considered to be at high metabolic risk. Eligibility criteria include resident in the UK, age > 18–< 50 years, BMI ≥ 23 kg/m^2^ (South Asian) or ≥ 25 kg/m^2^ (all other ethnicities), and plus one or more of the following: 1st degree relative with type 2 diabetes, previous gestational diabetes (GDM), previous baby > 4 kg, or high risk ethnicity for GDM. Eligible women who consent to participate will be enrolled in a commercially available preconception intervention (Prepare Plans, LiveSmart UK Ltd). Following an online health assessment and home blood test, women will be provided with individualised lifestyle advice and coaching by dietitians. Process evaluation will provide an assessment of implementation of the intervention. Change in health behaviours and biomarkers of metabolic health will also be examined.

**Discussion:**

Suboptimal health behaviours amongst women planning pregnancy are widely prevalent in the UK. Personalised health checks and coaching are especially important for women at risk of pregnancy complications. Get Ready! introduces a novel approach to identifying high risk women planning pregnancy and provision of a targeted intervention.

**Registration:**

Trial sponsor: King’s College London.

## Background

Health behaviours before pregnancy may profoundly influence pregnancy outcomes, and the future health of both mother and child, as detailed in a recent Lancet series [1]. The increasing awareness of health in the preconception period has been precipitated, at least in part, by the high prevalence of obesity amongst women at their first antenatal visit. Over half of women in the United Kingdom (UK) were overweight or obese in 2016–2017 [2], which increases the risk of adverse maternal, infant, and childhood outcomes and is a major burden to National Health Service (NHS) antenatal services and cost resources [3, 4]. This, together with the greater recognition that lifestyle changes are better made before, rather than during pregnancy has stimulated a shift in focus to strategies which promote healthier lifestyles amongst women contemplating pregnancy [1]. Aside from adverse influences on maternal body mass index, suboptimal nutrition per se is a common and modifiable cause of concern, as micronutrient deficiencies are implicated in fetal growth and development [5]. Data from the UK suggests that women of reproductive age are not nutritionally prepared for pregnancy, particularly younger women since they do not meet recommendations for micronutrient intakes including iron, iodine, and folate [1]. The benefit of folic acid supplementation in prevention of neural tube defects is indisputable [6], but in a recent survey of over 130,000 UK women planning pregnancy, we have shown that less than one third took folic acid supplements ([name], personal communication). Similarly, although the detrimental effects of smoking in pregnancy are widely known [7], 20% of women reported smoking in our survey ([name], personal communication).

Achieving readiness for pregnancy through appropriate preconception planning is key to optimising pregnancy outcomes for all women, with important consequences for maternal and child health. Surveys undertaken using the London Measure of Unplanned Pregnancy (LMUP) questionnaire suggest that pregnancy planning is common [8–10], although, currently, few NHS services target women planning pregnancy, with the majority of resources focusing on the antenatal period. NHS preconception care in the UK broadly falls within the remit of primary care and sexual health services [11]. Women planning pregnancy are often a difficult to reach group and are more likely to engage with health services once they become pregnant rather than before. Moreover, preconception care has been reported by primary care providers as being constrained by time and resources as well as competing with other preventative care [12]. Therefore, the first barrier to intervention is identifying women planning pregnancy.

Trials of interventions to improve health before conception are few [13] and use an unselected approach in targeting the general preconception population. Targeted personalised intervention in higher risk women planning pregnancy may be a more efficient and beneficial approach. Through an online recruitment process, this study will evaluate a novel approach to both identification of women planning pregnancy and those most at risk and examine whether a targeted intervention will improve health behaviours and markers of metabolic health.

## Methods

This protocol paper has been written following the SPIRIT guidance [14].

### Study aim

The aim of this study is to assess the feasibility of using an online recruitment process to identify high risk women planning pregnancy and examine health behaviours and biomarkers of metabolic health after a personalised intervention.

### Study objectives

To assess feasibility of linking users of a freely accessible online preconception tool via an online consenting process to an established preconception intervention.To estimate the rate of participation of women who are eligible to be enrolled into the study.To deliver a preconception intervention, informed by evidence-based lifestyle advice.To measure change in health behaviours including diet, physical activity, micronutrient supplementation, smoking, alcohol, and biomarkers of metabolic health.To perform a process evaluation.To use the data to determine participant numbers needed, intervention strategies, and methods of data collection and inform a primary outcome for a randomised controlled trial.

### Study design

This is a single-arm feasibility trial. A flow diagram is shown in Fig. 1.

**Fig. 1 Fig1:**
[figure not shown]
Study flow diagram

### Study population

The target population will be women planning a pregnancy considered to be at high risk as defined below.

### Study sample size

The sample size for the feasibility study is based on our objective to estimate the rate of participation of eligible women into the study. This study will recruit 55 women planning pregnancy. If we identify 110 eligible subjects, we will be able to estimate a participation rate of 50% to within a 95% confidence interval of ± 10% [15].

### Inclusion criteria

Women will be eligible for recruitment if they meet the following criteria:
Age > 18–< 50 yearsResident in the UKBody mass index (BMI) ≥ 23 kg/m^2^ (South Asian) or ≥ 25 kg/m^2^ (other ethnicities)

Plus one or more of the following:
1st degree relative with type 2 diabetesPrevious gestational diabetes mellitus (GDM)Previous baby > 4 kgHigh risk ethnicity for GDM including women from South Asian, Black Caribbean, and Middle Eastern ethnicities [16].

### Exclusion criteria

These include:
PregnancyResident outside the UKLow risk by the above criteria

### Participant recruitment

Women planning pregnancy will be identified from a free and widely used online preconception tool developed by Tommy’s, UK (www.tommys.org/pregnancy-information/planning-pregnancy/planning-for-pregnancy-tool). Users of the tool who leave their email address will receive an automated email inviting participation in the study via a link to the Get Ready! webpage. This webpage allows access to the study information leaflet, consent form, and a short screening questionnaire to assess eligibility. Women interested in participating, who meet the eligibility criteria, and who provide consent will be electronically enrolled to take part in an intervention to improve preconception health.

### Preconception intervention

Women will be directed to receive LiveSmart ‘Prepare Plans’, developed by NHS medical practitioners specifically for women planning a pregnancy (www.getlivesmart.com). The Plans combine online health assessment, blood tests, and personalised health coaching as appropriate for each woman, to optimise diet, preconception micronutrient supplementation, physical activity, and weight management and provide advice on smoking and alcohol reduction as necessary.

### Baseline assessment

The baseline assessment will consist of an online health questionnaire and blood profiling. The questionnaire will include social and demographic data (age, ethnicity, educational attainment, living environment), self-reported data on dietary intake, physical activity, alcohol consumption, smoking habits, anthropometry including weight and waist circumference, and any relevant medical history. For the blood sample, participants will be sent a home blood test kit to obtain a fasting blood sample (2 tubes of 0.5 ml and 0.8 ml) using a simple finger prick device with instructions. The blood sample will be posted to the diagnostic laboratory (County Pathology; http://www.countypathology.co.uk/) for assessment of lipid profile, HbA1c, thyroid function tests, renal function, liver function, and nutritional biomarkers. If abnormal results, e.g. raised HbA1c, are detected, women will be directed into clinical services. The data for the baseline assessment will be analysed by LiveSmart doctors and dietitians to devise individualised recommendations on preconception health improvement. The participants receive a personal health report.

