### Outcomes

*Change in self-report health behaviours to include:*
Weight/BMIDietary intakePhysical activity levelsSmoking statusAlcohol consumptionSupplementation with folic acid 400 μg/5 mg, vitamin D 10 μg*Change in biomarkers of metabolic health to include:*
Lipid profileHbA1cNutritional biomarkers including vitamin D, folate, vitamin B_12_, ferritin*Feasibility and process evaluation to include:*
The efficiency of the online recruitment system.Recruitment and retention:
Proportion of women who are eligible to take part in the intervention.Time to recruit 55 women.Loss to follow-up.Adequacy of 3-month timeframe to facilitate change in health behaviours and metabolic health.Dose delivered and dose received (the proportion of intended intervention received).Acceptability (if the intervention including online health assessment, home blood test kit, health coaching, intervention materials were well received by participants). Participating women will be asked to complete a digital questionnaire where they rate acceptability of the intervention components on a Likert scale.

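### Treatment obtained outside the programme after a baseline referral may enter the uncontrolled 12-week change in HbA1c and lipids, and the article states no way to separate it

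*Protocol article*

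**What the plan says.** The order of events in the protocol article is as follows.

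- **Enrolment (Participant recruitment).** Women "who meet the eligibility criteria, and who provide consent will be electronically enrolled to take part in an intervention". Eligibility is judged on a screening questionnaire, so no blood result is known at this point.
- **Exclusions (Exclusion criteria).** The section names pregnancy, living outside the UK and being low risk. It names neither known diabetes, nor a raised HbA1c, nor current glucose- or lipid-lowering treatment.
- **Blood test and referral (Baseline assessment).** A home sample is tested for lipids, HbA1c, thyroid, renal and liver function, and nutritional markers. "If abnormal results, e.g. raised HbA1c, are detected, women will be directed into clinical services".
- **Follow-up (Follow-up assessment).** The online questionnaire is repeated and a blood sample is taken when the 12-week intervention ends.
- **Outcomes.** The list headed "Change in biomarkers of metabolic health to include" names the lipid profile, HbA1c and nutritional biomarkers. Referral and its uptake are not among the process outcomes.
- **Analysis.** Follow-up of every participant will be attempted. Change is analysed by linear and logistic regression, with the adjustment variables left open.
- **Design and use.** "This is a single-arm feasibility trial". One objective is "To use the data to determine participant numbers needed" and to inform the primary outcome of a randomised trial. The Discussion says the pre-to-post comparison will settle whether the strategy can bring about better health in these women.

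**The concern.** The cohort is selected for diabetes risk, so some raised HbA1c results are foreseeable; the article itself uses raised HbA1c as its example. Referral follows the baseline test, and HbA1c and lipids are outcomes 12 weeks later. Any treatment begun promptly by clinical services would fall inside the measurement window. It would fall on the women with the highest baseline values, who are also the most prone to regression to the mean.

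With no control arm, nothing in the design absorbs such an effect. Two uses of the change data are exposed: the Discussion's conclusion about whether the strategy works, and the mean and SD of change carried into planning the randomised trial. If outside treatment is not recorded during follow-up, no later analysis can separate it.

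**Working it through.** **1. The plan's own figure.** The only sample-size figure concerns participation: 110 eligible women, a rate of 50% and a 95% interval of ±10 percentage points. The half-width is 1.96 × √(0.5 × 0.5 / 110) = 0.093, or ±9.3 points, and 50% of 110 is 55. The figure reproduces; 97 eligible women would be the minimum for ±10 points. It says nothing about the precision of biomarker change, so it neither supports nor answers the concern.

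**2. Inputs for an illustration.** From the article: 55 women ("This study will recruit 55 women planning pregnancy"), a single arm, 12 weeks. Assumed, because the documents give no values: share of women treated after referral, 2% to 20%; added HbA1c fall in those women, 5 to 15 mmol/mol, reached by 12 weeks; SD of change otherwise, 3 to 5 mmol/mol.

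**3. Shift in the mean** = share treated × added fall.

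| Share treated | Women of 55 | Fall 5 | Fall 10 | Fall 15 |
|---|---|---|---|---|
| 2% | 1.1 | 0.10 | 0.20 | 0.30 |
| 5% | 2.8 | 0.25 | 0.50 | 0.75 |
| 10% | 5.5 | 0.50 | 1.00 | 1.50 |
| 20% | 11.0 | 1.00 | 2.00 | 3.00 |

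**4. Sampling error of the mean change at n = 55** = 1.96 × SD / √55.

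- SD 3: 1.96 × 3 / 7.416 = 0.79 mmol/mol.
- SD 5: 1.96 × 5 / 7.416 = 1.32 mmol/mol.

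The shift of 0.1 to 3.0 therefore runs from well below to well above the half-width. Treated women also widen the SD, so the top corner needs a check. With 20% treated, a fall of 15 and SD 5, the variance is 25 + 0.2 × 0.8 × 225 = 61, the SD is 7.81 and the half-width is 1.96 × 7.81 / 7.416 = 2.06. The shift of 3.0 still exceeds it.

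**5. With losses to follow-up.** If 44 of 55 women give a second sample (assumed), 3 treated women with a fall of 10 shift the mean by 3 × 10 / 44 = 0.68. Five treated women with a fall of 15 shift it by 5 × 15 / 44 = 1.70.

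**6. Effect on the SD of change.** Take the milder case in step 5, with SD 3 and no change in the other women. With p = 3/44 = 0.068, the variance is 9 + 0.068 × 0.932 × 100 = 15.35, so the SD is 3.92 rather than 3.00. For a fixed target difference, sample size is proportional to variance: 15.35 / 9 = 1.71 and 9 / 15.35 = 0.59. Which SD is right depends on the randomised trial. If it excludes these women, planning on 3.92 oversizes it by a factor of 1.71. If it enrols and refers them in the same way, planning on 3.00 gives only 59% of the number needed.

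**The case against.** Several counterarguments carry weight.

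- **Referral is not treatment.** The article does not say that treatment starts, or when, or that referred women stay in the analysis. Their inclusion is a fair inference from the exclusion, outcome and analysis sections, but it is not written, and the exclusion list is introduced in words that do not make it exhaustive. A reader might infer that treatment effects will certainly be reported as effects of coaching. The documents support only that they may contribute.
- **Some recording may already exist.** The questionnaire covers relevant medical history and is repeated at 12 weeks, so it may pick up new treatment. The article does not show that it asks about treatment started or changed since baseline.
- **Detail may sit elsewhere.** Handling of concomitant treatment is often left to a full protocol or analysis plan, neither of which is shown. This argues against calling the open adjustment wording an error. It does not remove the need to collect the data before follow-up closes.
- **Including referred women can be right.** If referral after the programme's own test is part of the strategy, the all-women change is a legitimate treatment-policy estimate. The article does not say which reading is meant.
- **The scope is narrower than it looks.** A reader might extend the point to thyroid, renal and liver tests, but these are not listed outcomes and their repetition is not stated. Higher-dose vitamin D advised by the programme's own doctor belongs to the intervention.
- **The consequence is limited.** This is a feasibility study sized on participation, and a single-arm change could not be attributed to coaching in any case. Referral adds one source of confounding to others already present.

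**Conclusion.** The point stands in a limited form. Referral is triggered after enrolment, and no stated step removes or separates the referred women. HbA1c and lipid change is uncontrolled and is put to two uses that outside treatment could distort.

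The size cannot be determined from the documents. The illustrated shift of 0.1 to 3.0 mmol/mol in mean HbA1c, against a half-width of 0.8 to 1.3, rests wholly on assumed referral shares, treatment effects and SDs, and on the effect appearing within 12 weeks. It shows only that the matter may be trivial or may exceed sampling error, and that without recording nobody could tell which.

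A reader might also infer that the randomised trial would come out about 1.7 times too large, or that the estimate from untreated women is the one to carry forward. Neither follows. The first assumes a randomised trial without these women. The second conditions on an event after baseline, removes the highest baseline values and could undersize a trial that enrols and refers the same women.

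**What to change.** 1. Make sure the 12-week questionnaire asks explicitly whether a clinical referral was taken up, and whether any glucose- or lipid-lowering treatment was started or changed since baseline.
2. Count referrals as a process outcome.
3. Report the mean and SD of change in HbA1c and lipids for all women. As a sensitivity analysis, repeat this excluding women whose treatment was started or changed, and state that this subset is selected after baseline.
4. For sizing the randomised trial, use the SD that matches its intended population and its handling of referrals. Do not fix the untreated-only estimate in advance.
5. In the Discussion, limit the conclusion to change after the programme including any referral, without attributing it to coaching.

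The cost is one or two questionnaire items, one extra set of estimates and a sensitivity estimate that is slightly less precise because it rests on fewer women. No change to the referral rule is proposed.

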### Health coaching

Individualised health coaching, delivered by dietitians by telephone over 12 weeks, will target modifiable preconception risk factors and provide ongoing support to improve health. The health coaching will include 1 starter session (50 min), plus 4 follow-up sessions (20 min). Throughout the coaching, each participant will be encouraged to identify areas which would benefit from change and as such is highly personalised.

The health coaching will focus on:
Achieving sustainable weight reduction via lifestyle changes in dietary intake and physical activity.Improving dietary intake and physical activity in line with UK national recommendations.Appropriate supplementation for women planning pregnancy. Participants will be encouraged to take folic acid (400 μg) and vitamin D (10 μg) supplements in line with national guidelines. Participants will have the option of LiveSmart providing supplements free of charge (Vitl; https://vitl.com). If a woman has a BMI ≥ 30 kg/m^2^, they will be directed to their GP to obtain folic acid 5 mg as per clinical guidance. If a woman has a detected vitamin D deficiency or insufficiency, they will be advised to take a higher dose of vitamin D by the LiveSmart doctor.Smoking reduction if appropriate.Alcohol reduction if appropriate.

Participants will be encouraged to set achievable goals which will be reviewed in follow-up sessions. Participants will also be encouraged to identify potential barriers to implementation of their lifestyle goals and will be assisted to problem solve and develop strategies to facilitate their successful implementation. Following each phone call, participants will be provided with a summary of the call and the agreed goals. They will also be provided with relevant resources such as helpful apps or webpages, recipe ideas, and physical activity challenges. The summaries and resources will be available to participants via the LiveSmart user app.

### Follow-up assessment

The follow-up assessment will include the online health questionnaire and a blood sample at the end of the 12-week intervention.

### Outcomes

*Change in self-report health behaviours to include:*
Weight/BMIDietary intakePhysical activity levelsSmoking statusAlcohol consumptionSupplementation with folic acid 400 μg/5 mg, vitamin D 10 μg*Change in biomarkers of metabolic health to include:*
Lipid profileHbA1cNutritional biomarkers including vitamin D, folate, vitamin B_12_, ferritin*Feasibility and process evaluation to include:*
The efficiency of the online recruitment system.Recruitment and retention:
Proportion of women who are eligible to take part in the intervention.Time to recruit 55 women.Loss to follow-up.Adequacy of 3-month timeframe to facilitate change in health behaviours and metabolic health.Dose delivered and dose received (the proportion of intended intervention received).Acceptability (if the intervention including online health assessment, home blood test kit, health coaching, intervention materials were well received by participants). Participating women will be asked to complete a digital questionnaire where they rate acceptability of the intervention components on a Likert scale.

### Analysis

Retention will be estimated from recruitment rate, consent rate, withdrawal, and loss to follow-up. For summary statistics, binary and categorical variables will be presented using counts and percentages. The distribution of continuous variables will be assessed using coefficients of skewness and then summarised by mean and standard deviation (SD) or median and interquartile range (IQR) where appropriate. To assess the change in health behaviours (dietary intake, physical activity, weight, smoking, alcohol) and biomarkers of metabolic health, linear and logistic regression will be utilised, with appropriate adjustment. To maintain sample size and power, we will attempt to follow-up all participants; however, if there is missing data present, we will assess the type of missing data and perform the appropriate sensitivity analyses. The data analysis will be performed in Stata (StataCorp LP, College Station, Texas) 16.0.

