## Discussion

The health of the mother before conception can profoundly influence the risk of complications in pregnancy and may adversely affect the lifelong health of the child [17]. We have found in a large-scale survey that UK women are not adequately prepared for pregnancy. There is no easy way to identify women planning pregnancy and few NHS services to support positive lifestyle behaviour modifications despite enormous demand for advice by this demographic. In addition, targeting women with modifiable risk factors before pregnancy may be a more efficient and beneficial approach.

This study will determine whether it is achievable to link digital tools to identify high risk women planning a pregnancy with a preconception health optimisation programme. Examining change in health behaviours and biomarkers of metabolic health pre- and post-a personalised intervention will determine whether this strategy can improve health in high risk women in the preconception period.

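### The Discussion promises a verdict on benefit from unranked before-after changes, in a study sized only for the participation rate

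*Protocol article*

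**What the plan says.** All references are to the protocol article.

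- **Design and size.** Study design: "This is a single-arm feasibility trial". The section on sample size explains: "The sample size for the feasibility study is based on our objective to estimate the rate of participation of eligible women into the study". It adds this precision statement: "If we identify 110 eligible subjects, we will be able to estimate a participation rate of 50% to within a 95% confidence interval of ± 10" percentage points. The recruitment target of 55 is half of those 110. No change from baseline is sized or powered.
- **Outcomes.** The changes in behaviours and biomarkers come first and the feasibility measures after them. Nothing is called primary, secondary or exploratory.
- **Analysis.** "To assess the change in health behaviours (dietary intake, physical activity, weight, smoking, alcohol) and biomarkers of metabolic health, linear and logistic regression will be" used. The section gives no lead outcome, order or significance level for these changes. It does speak of preserving power.
- **Discussion.** Examining the changes before and after the intervention "will determine whether this strategy can improve health in high risk women in the preconception period". The end of the Background has a matching phrase: the study is to look at whether a targeted intervention improves behaviours and metabolic markers.
- **Study objectives, last item.** "To use the data to determine participant numbers needed, intervention strategies, and methods of data collection and inform a primary outcome for a randomised controlled" study to follow.

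**The concern.** The sample-size section and the Discussion describe two different studies. The first estimates a proportion. The second reaches a conclusion on benefit from a set of changes that were neither sized nor ranked. Those changes can disagree: serum folate might rise while weight and HbA1c stay put. The document does not say which of them would then settle whether health improved, so the claim could rest on whichever change happened to look favourable.

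The same data are also to feed the planning of a randomised trial. If its outcome or target difference were taken from the change that looked best here, selection would inflate that difference and the later trial would be too small. The ranking problem is separate from the lack of a control group and would remain if there were one.

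**Working it through.** **1. The plan's own figure.** Inputs: 110 eligible women, 50% participation (Study sample size). The 95% half-width is 1.96 × √(0.5 × 0.5 / 110) = 0.093. The exact interval for 55/110 is 40.3% to 59.7%, a half-width of 9.7 points. The stated ± 10% is reproduced and not in dispute. It is the only precision statement in the document.

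**2. How many changes.** From Outcomes:
- behaviours: weight/BMI, diet, activity, smoking, alcohol = 5
- supplements: folic acid, vitamin D = 2
- biomarkers: lipid profile (a panel, counted once), HbA1c, vitamin D, folate, vitamin B12, ferritin = 6

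Total 5 + 2 + 6 = 13. The sentence in Analysis does not mention supplements, so on that sentence alone the count is 5 + 6 = 11.

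**3. Chance of at least one nominal improvement when nothing has changed.** Assumption: each change is judged at two-sided 5%, so 2.5% in the improving direction.

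If independent, the chance is 1 − 0.975^k:
- k = 13: 1 − 0.7195 = 28.1%
- k = 11: 1 − 0.7569 = 24.3%
- one pre-named outcome: 2.5%

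For correlated outcomes, 200,000 draws of normal test statistics with a common correlation give:

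| Correlation | 11 changes | 13 changes |
|---|---|---|
| 0 | 24% | 28% |
| 0.3 | 19% | 21% |
| 0.5 | 15% | 17% |
| 0.7 | 11% | 12% |

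The document gives no correlations, so the whole range is shown. The conclusion is the same for 11 or 13.

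**4. Illustration for the randomised trial.** Assumptions not in the document: a true standardised change of 0.20 in all 13 outcomes, 55 women with complete data, and the largest observed change used as the planning value. Its expected value is 0.20 + E(max z)/√55:
- correlation 0.5: 0.20 + 1.182/7.416 = 0.36
- independent: 0.20 + 1.668/7.416 = 0.42

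A study sized for 90% power on that value has, at the true 0.20, power Φ(3.24 × 0.20/0.359 − 1.96) = 44% or Φ(3.24 × 0.20/0.425 − 1.96) = 33%. This shows the direction and rough size of selection bias if that route were taken. It does not describe what the authors plan.

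**The case against.** The strongest reply is that this is a feasibility study and reads like one. The aim puts feasibility first, the abstract says the changes will also be examined, and the sample size rests on participation alone. A single-arm feasibility study needs no efficacy primary outcome and no multiplicity adjustment if its changes are descriptive. A ranking of outcomes may sit in a full protocol or analysis plan that is not shown. All of this stands, and a missing hierarchy by itself would not be a finding. What it does not answer is the sentence in the Discussion, echoed in the Background, which does not treat the changes as descriptive.

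Three stronger readings are tempting but not supported:

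- **That the randomised trial will be built on the largest change.** The objective says only that the data will "inform a primary outcome for a randomised controlled trial" and determine its numbers. Participation, retention and standard deviations could serve both purposes. No selection rule is stated.
- **That the relevant error is the two-sided one**, 24% to 49% for 13 changes at correlations from 0.7 down to 0. That counts chance deterioration, whereas the harm at issue is a false claim of improvement.
- **That at least 13 changes are analysed.** Thirteen comes from the Outcomes list with the two supplements counted separately. The Analysis sentence names about 11.

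It is also fair to say that the lack of a comparator defeats the Discussion sentence on its own: even one pre-named change could not show that the strategy improves health.

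**Conclusion.** The point holds as an overstated conclusion, not as a missing multiplicity rule. The document commits to settling whether the strategy can improve health from 11 to 13 unranked changes, with a sample size chosen for something else and no outcome that decides when they disagree. The chance of at least one nominal improvement among 13, with no true change, is about 12% to 28%, against 2.5% for one named in advance. This rests on an assumed two-sided 5% level for each change, on correlations between 0 and 0.7, and on treating the yes/no outcomes as approximately normal test statistics. Planning the randomised trial on a selected change is a risk that the last objective leaves open, and the figures for it are illustrative only. The change is worth making because it alters what the study may conclude and costs almost nothing.

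**What to change.** 1. **Outcomes and Analysis:** name the participation rate among eligible women as the primary outcome. It already sets the sample size but is not plainly listed; the nearest item concerns the proportion who are eligible.
2. **Same sections:** label every behaviour and biomarker change exploratory, and report each one with its estimate and 95% confidence interval, whichever way it moved. No multiplicity correction is then needed.
3. **Discussion, and the matching phrase in the Background:** reword so that no conclusion of benefit is drawn from the changes.
4. **Last objective:** state that this study supplies standard deviations, before-after correlations, completeness and retention, and that the randomised trial's primary outcome and target difference will be set on clinical relevance and measurability.

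The cost is a few sentences, with no extra data or participants. The downside is that the study gives up a claim of improvement that it was not sized to support.
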